#### Analysis plan

The analysis and presentation of results will be in line with the Consolidated Standards of Reporting Trials (CONSORT) Statement for cluster randomised controlled trials [62]. Descriptive statistics of demographic and outcome measures at baseline will be tabulated to ascertain any imbalance between arms.

The main analysis of the primary and secondary outcomes will be based on cross-sectional analyses that will compare the outcome at endline between the control arm and each of the intervention arms. All analysis will be carried out on groups as randomised (‘intention to treat’). All analyses will account for the nature of the distribution of the relevant outcome, and results will be presented as appropriate effects sizes (difference in means between arms; odds ratios) with a measure of precision (95% confidence intervals). Generalised estimating equations will be used to account for clustering. Analyses will adjust for baseline by inclusion of the cluster mean of the outcome as a covariate in statistical models.

Unadjusted and adjusted results will be presented for all analyses. Covariates in adjusted analyses will be specified *a priori* and will include the strata (distance to the nearest town and proportion of Scheduled Castes/Scheduled Tribes).

This is a multi-arm trial and, to restrict the number of comparisons, no statistical comparisons will be made directly between intervention arms. We will restrict formal testing, and reporting of *p* values, to the primary and secondary outcomes and will only compare each of the intervention arms with the control arm. Thus, no formal adjustment for multiple comparisons will need to be made. All other outcomes will be reported and interpreted with caution.

Planned subgroup analyses will include the impact of mothers’ exposure to the interventions, caste, and wealth. All subgroup analyses will be performed by including a variable (or variables, as appropriate) for the subgroup and its interaction with the treatment in the model. Results will be interpreted with due caution. Full details of all analyses, including any additional covariates to be included in the adjusted models, will be set out *a priori* in a Statistical Analysis Plan that will be uploaded as an appendix prior to the start of the endline survey.

As we will conduct repeat cross-sectional surveys to assess the trial outcomes, loss to follow-up of specific individuals is not an issue. Questionnaire completion rates are expected to be high, so only a small proportion of missing data is expected, and it is unlikely that it will have to be accounted for in any analysis. Sensitivity analyses (such as best- and worst-case scenarios and inverse probability weighting) will be conducted for the primary outcomes.

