## Methods/design

### Study aim

This study aims to estimate the nutritional and agricultural impacts and cost-effectiveness of (1) an agricultural extension platform of women’s groups viewing and discussing videos on NSA practices, with visits at women’s homes or farms to follow up on adoption of new practices shown in the videos (AGRI), (2) women’s groups viewing and discussing videos on NSA and nutrition-specific practices, also with follow-up visits (AGRI-NUT), and (3) women’s groups viewing and discussing videos on NSA combined with a PLA approach of meetings and nutrition-specific videos, with follow-up visits (AGRI-NUT+PLA). These three interventions will be compared to a control arm that does not receive these interventions, but might receive, along with the treatment arms, standard agriculture-, health- and nutrition-related services provided by the government or other organisations. Government frontline health and nutrition workers (*Anganwadi* workers and Accredited Social Health Activists) in all arms, including the control arm, will receive 2 days of training on nutrition.

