#### Assessing fidelity and quality of the intervention’s implementation

We will report data on three domains related to fidelity and quality of implementation in the main trial results paper. First, we will assess intervention workers’ *knowledge* of NSA (all intervention arms) and maternal, infant, and young child nutrition (in the AGRI-NUT and AGRI-NUT+PLA arms), as well as their facilitation skills. We will test intervention workers’ knowledge during the implementation period and calculate average test scores per arm. Second, we will assess the *quality* of video disseminations and PLA meetings (AGRI-NUT+PLA), including quality of facilitation, through structured observation forms (all intervention arms). Finally, we will measure intervention *coverage* and exposure by arm, as specified below:Percentage of pregnant woman and mothers of children younger than 2 years in the endline survey who are members of SHGsPercentage of planned intervention events that were actually implementedPercentage of pregnant woman and mothers of children younger than 2 years who have attended/received any planned intervention activities (video disseminations, PLA meetings, home visits) in the 6 months before the start of the endline surveyMean number of total intervention activities (video disseminations, PLA meetings, follow-up visits) attended/received by women in the last 6 months before the start of the endline survey

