##### Assessment of component activation

We will gather information from the interventions’ monitoring systems, the endline survey, and qualitative data described below to conduct a systematic assessment of the components activated by the interventions, using the theory of change as a guide. If the final trial analyses detect no effect on the primary and secondary outcomes, this systematic assessment will also allow us to investigate what shortcomings may have compromised the interventions’ effects.

We will use quantitative and qualitative data sources for the assessment. The intervention monitoring systems and endline survey provide data on exposure to the interventions. The trial’s endline survey also provides data on other intermediate outcomes in the theory of change. To further understand women’s experiences of, and responses to, the intervention, we will conduct semi-structured interviews with pregnant women (*n* = 5), mothers of children younger than 2 years (*n* = 5), their husbands (*n* = 10), and mothers-in-law (*n* = 10) per arm, or around a total of 30 interviews in each of the three intervention arms. Participants will be sampled purposively to represent the mix of caste and tribal groups present in the intervention areas. We will supplement the interviews with participant observations in a subsample of three participant observations per arm.

We will conduct around four focus group discussions per arm with women’s groups to understand reasons for attendance patterns, the groups’ ability to plan and implement strategies together, and dissemination of information beyond the group. We will sample women’s groups purposively, based on the trial strata and their longevity. We will also conduct two focus group discussions per arm with the frontline UPAVAN implementation staff to understand factors that supported or hindered the interventions’ implementation. We may also conduct one focus group discussion per arm with key government frontline health and nutrition workers.

We will collect data in two waves of around 3 months each, and may sample additional women or use new data collection techniques if analyses generate questions that require further exploration. A data collection group independent of the implementation team will collect the qualitative data. We will use a thematic approach to data analysis in order to capture themes related to the theory of change and other emergent themes.

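### Mothers' exposure to the interventions is planned as a subgroup with a treatment interaction, but exposure arises after allocation and is absent by design in controls, so the interaction is not identified if exposure means attendance or receipt

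*Protocol article*

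**What the plan says.** The Analysis plan section of the protocol article names three planned subgroup analyses: mothers' "exposure to the interventions, caste, and wealth". It then sets a common method: "All subgroup analyses will be performed by including a variable (or variables, as appropriate) for the subgroup and its interaction with the treatment". The same section says that formal testing "will only compare each of the intervention arms with the control arm" and that "no statistical comparisons will be made directly between intervention arms". It also commits to analysing every cluster in the arm to which it was allocated. Subgroup results are to be read cautiously, and full analysis details are left to a statistical analysis plan.

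The Study aim section describes "a control arm that does not receive these interventions". The process evaluation (Assessing fidelity and quality of the intervention's implementation) measures coverage and exposure by arm, including the percentage of women who have "attended/received any planned intervention activities" in the six months before the endline survey. Under Assessment of component activation the protocol adds: "The intervention monitoring systems and endline survey provide data on exposure to the interventions". Under Intended coverage, follow-up visits go to women who attended meetings, and non-attenders are encouraged to come.

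**The concern.** A subgroup analysis by interaction asks whether the effect of allocation differs between kinds of people who exist in both arms. The subgroup variable therefore has to be defined in both arms and unaffected by allocation. Attendance meets neither condition. A control mother has nothing to attend, and an intervention mother's attendance is something she chooses after her cluster has been allocated.

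Two things are at stake. First, a planned analysis may not be computable as written. Software will typically drop a redundant column, and what is then labelled a subgroup effect is something else. Second, what remains is a comparison of self-selected women with an unselected control arm. Women who attend may differ in diet, time or motivation. A difference between them and all controls could look like a benefit in those reached, or like a dose-response, with no intervention effect behind it. It would also sit in a list of planned subgroup analyses, which lends it credibility.

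**Working it through.** **The plan's own figures.** Sample size section: 37 clusters per arm, 24 children aged 6–23 months per cluster, ICC 0.06, 22% against 31%. Design effect = 1 + (24 − 1) × 0.06 = 2.38. Effective size per arm = 37 × 24 / 2.38 = 373.1. Two-sided 5% power = 79.7%, against 80% stated. The sample size reproduces and is not in dispute; 22% and 9 points are used below as reference values.

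**Is the interaction identified?** For one intervention arm against control, let T be allocation and E be exposure. The stated model has columns 1, T, E and T×E.

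- Controls: T = 0 and E = 0, so T×E = 0 = E.
- Intervention arm: T = 1, so T×E = E.

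E and T×E are equal in every row. With 37 × 32 = 1,184 dyads per arm the matrix has rank 3 of 4. This is a property of the columns, so neither a logit link nor generalised estimating equations change it. Fitting all four arms together does not rescue it: the three arm-by-exposure columns sum to E. The only exposure contrasts then available are between intervention arms, which the plan rules out. By comparison, a baseline subgroup with 50% prevalence in both arms gives rank 4 of 4.

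**If a few controls are exposed.** In outcome SD units and ignoring clustering, SE(interaction) = √(sum of 1/n over the four T-by-E cells). Assume half of the intervention arm is exposed (592 and 592).

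| Exposed controls (assumed) | Calculation | SE |
|---|---|---|
| 12 (1%) | √(2/592 + 1/12 + 1/1172) | 0.30 |
| 24 (2%) | √(2/592 + 1/24 + 1/1160) | 0.21 |
| 59 (5%) | √(2/592 + 1/59 + 1/1125) | 0.15 |
| Balanced baseline subgroup | √(4/592) | 0.08 |

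The term can then be fitted, but it depends on a handful of unusual control women and is still self-selected on both sides.

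**What is left after a column is dropped.** The T coefficient becomes non-attenders minus all controls, and the E coefficient becomes attenders minus non-attenders. Their sum is attenders minus all controls.

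**How large could the bias be?** The documents give neither attendance nor strength of selection, so both are assumed. Under no true effect, the attenders' prevalence pe and the non-attenders' prevalence pn satisfy a·pe + (1 − a)·pn = 0.22, with odds ratio OR between them and attendance a. Differences from 22%, in percentage points (attenders / non-attenders):

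| OR | a = 30% | a = 40% | a = 50% |
|---|---|---|---|
| 1.5 | +5.06 / −2.17 | +4.24 / −2.83 | +3.46 / −3.46 |
| 2.0 | +8.82 / −3.78 | +7.28 / −4.85 | +5.83 / −5.83 |
| 2.5 | +11.78 / −5.05 | +9.60 / −6.40 | +7.60 / −7.60 |

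Two of the nine scenarios exceed the 9-point target.

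A second illustration uses a shared latent trait that raises the log-odds of both attendance and outcome by 0.25, 0.5 or 0.75 per SD, with attendance of 30 to 70%. Simulated prevalence in attenders runs from 22.35% to 27.77%, which is +0.4 to +5.8 points over 22%. All of these lie below 9.

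**The case against.** The strongest reply has four parts.

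*Exposure is not defined in the Analysis plan.* The process evaluation's list of coverage and exposure measures begins with membership of self-help groups. These are savings groups that often predate the trial and can exist in control clusters; with that measure the model has full rank. This stands as a condition on the claim. A reader might infer that the interaction is impossible under any definition, and the documents do not support that. Attendance or receipt is nevertheless the natural meaning of exposure to the interventions, and endline group membership could itself be affected by allocation, because new groups are formed where none exist.

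*Zero exposure in controls is a design statement, not a measurement.* This also stands. The protocol takes steps against contamination across arms but does not guarantee that there is none. The consequence is the unstable model shown above, not a sound one.

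*The analysis plan will supply details, and results will be read with caution.* This does not answer the point. The protocol has already named exposure as a subgroup and fixed the model for every subgroup; a later document could repair it only by departing from that. Caution neither identifies the term nor removes selection.

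*The bias figures are assumed.* Correct. The size is illustrative, and so is the direction: facilitators seek out women who do not attend, so positive selection is plausible but not established. The protocol does not specify the attender-versus-control fallback either. A reader might take +11.8 and −7.6 points as a matching pair, but they come from different scenarios (30% and 50% attendance).

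**Conclusion.** The point holds on the reading that exposure means attendance at, or receipt of, intervention activities. With no exposed controls the planned interaction is not identified for any arm against control (rank 3 of 4). With 1 to 5% of controls exposed it is estimable, with a standard error roughly two to four times that of a balanced baseline subgroup, and still confounded by self-selection. The likely substitute departs from the plan's own principle of analysing by allocated group. It could show a false effect of about +0.4 to +11.8 points across the two assumed selection models, against a 9-point target.

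A reader might infer that the trial's main result is compromised. It is not: the primary and secondary comparisons are by allocated arm, the sample size reproduces, and no primary or secondary comparison depends on this analysis. It is a should-fix item.

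**What to change.** Delete mothers' exposure from the planned subgroups. Keep the interaction model for characteristics fixed before allocation or unaffected by it. Caste qualifies. Wealth qualifies only if it is measured so that the intervention cannot change it, which needs stating because household income is one of the hypothesised pathways and the endline survey is a fresh cross-section. Report exposure descriptively by arm, as the process evaluation already plans.

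If an effect of receipt is wanted, a complier-average analysis for each arm against control, with allocation as the instrument, can be added as optional and exploratory. It should say that spillover to non-attenders would violate its exclusion assumption. Spillover is part of this design: participatory groups are meant to share what they learn with the wider community, and the process evaluation studies how information travels beyond the group. Such an estimate would also be imprecise.

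The cost is one sentence in the protocol and in the analysis plan. Nothing that could be validly estimated is lost.

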#### Adverse events

We do not expect any adverse effects of the intervention, but the trial will be monitored for severe adverse events. Information on these events is collected and compiled on a quarterly basis. The principal investigator will review the quarterly severe adverse events report to assess the level of relatedness to intervention. These data, with allocation concealed, will be shared annually with the independent statistician on the Trial Steering Committee for review. If any problems arise, the Trial Steering Committee can request the data to be unblinded. The independent statistician will share his/her assessment in writing with the Trial Steering Committee and research team.

### Process evaluation

Our process evaluation has three objectives: (1) to assess the fidelity and quality of the interventions’ implementation, (2) to clarify mechanisms behind the intervention’s effect, and (3) to identify contextual factors associated with variation in effects on the primary outcomes.

#### Assessing fidelity and quality of the intervention’s implementation

We will report data on three domains related to fidelity and quality of implementation in the main trial results paper. First, we will assess intervention workers’ *knowledge* of NSA (all intervention arms) and maternal, infant, and young child nutrition (in the AGRI-NUT and AGRI-NUT+PLA arms), as well as their facilitation skills. We will test intervention workers’ knowledge during the implementation period and calculate average test scores per arm. Second, we will assess the *quality* of video disseminations and PLA meetings (AGRI-NUT+PLA), including quality of facilitation, through structured observation forms (all intervention arms). Finally, we will measure intervention *coverage* and exposure by arm, as specified below:Percentage of pregnant woman and mothers of children younger than 2 years in the endline survey who are members of SHGsPercentage of planned intervention events that were actually implementedPercentage of pregnant woman and mothers of children younger than 2 years who have attended/received any planned intervention activities (video disseminations, PLA meetings, home visits) in the 6 months before the start of the endline surveyMean number of total intervention activities (video disseminations, PLA meetings, follow-up visits) attended/received by women in the last 6 months before the start of the endline survey

#### Clarifying mechanisms behind the interventions’ effects

We will explore mechanisms behind the interventions’ effects through two main methods: (1) an assessment of which intervention components were activated, and which were not, using the theory of change; (2) mediation analyses.

##### Assessment of component activation

We will gather information from the interventions’ monitoring systems, the endline survey, and qualitative data described below to conduct a systematic assessment of the components activated by the interventions, using the theory of change as a guide. If the final trial analyses detect no effect on the primary and secondary outcomes, this systematic assessment will also allow us to investigate what shortcomings may have compromised the interventions’ effects.

We will use quantitative and qualitative data sources for the assessment. The intervention monitoring systems and endline survey provide data on exposure to the interventions. The trial’s endline survey also provides data on other intermediate outcomes in the theory of change. To further understand women’s experiences of, and responses to, the intervention, we will conduct semi-structured interviews with pregnant women (*n* = 5), mothers of children younger than 2 years (*n* = 5), their husbands (*n* = 10), and mothers-in-law (*n* = 10) per arm, or around a total of 30 interviews in each of the three intervention arms. Participants will be sampled purposively to represent the mix of caste and tribal groups present in the intervention areas. We will supplement the interviews with participant observations in a subsample of three participant observations per arm.

We will conduct around four focus group discussions per arm with women’s groups to understand reasons for attendance patterns, the groups’ ability to plan and implement strategies together, and dissemination of information beyond the group. We will sample women’s groups purposively, based on the trial strata and their longevity. We will also conduct two focus group discussions per arm with the frontline UPAVAN implementation staff to understand factors that supported or hindered the interventions’ implementation. We may also conduct one focus group discussion per arm with key government frontline health and nutrition workers.

We will collect data in two waves of around 3 months each, and may sample additional women or use new data collection techniques if analyses generate questions that require further exploration. A data collection group independent of the implementation team will collect the qualitative data. We will use a thematic approach to data analysis in order to capture themes related to the theory of change and other emergent themes.

##### Mediation analyses

We will explore the role of four hypothesised mediators of the effects of the interventions on maternal and child nutrition: agricultural production, household income, women’s workload, and women’s decision-making. Data on these potential mediators will be captured by the endline survey. We will explore, if appropriate, the role of these mediators through causal mediation analyses using the potential outcomes framework [63].

#### Identifying contextual factors associated with variations in outcomes

In addition to the pre-specified subgroup analyses, as a part of the process evaluation we will explore the role of other factors such as women’s group longevity associated with primary and secondary outcomes.

### Economic evaluation

The economic evaluation will be conducted from a societal perspective, taking into account all costs incurred by the implementing agencies (program costs), community and health care providers, and users or households, and all associated and measurable outcomes or benefits associated with the intervention.

The program costs will be estimated using a combination of activity-based costing and an ingredients approach [64]. Program costs will be collected prospectively from the project accounts of all implementing partners. These costs will be entered into an MS Excel data capture tool designed for this purpose. Costs incurred by government frontline workers and community level institutions such as *gram panchayat* (local, elected body of representatives) and health facilities will be collected retrospectively using key informant interviews and publicly available salary information. Costs incurred by households affected by the UPAVAN interventions will be collected using household surveys.

All costs will be estimated from an economic perspective, assessing the full impact on all parties of direct and indirect costs, including time costs and donated goods. All costs will be adjusted for inflation using the Indian Consumer Price Index and converted to International Dollars to adjust for purchasing power parity.

The economic evaluation will take the form of a cost-consequence analysis, comparing incremental costs of the interventions and incremental changes in the trial outcomes [65]. Incremental costs and significant outcomes will be listed separately, allowing policymakers to compare the incremental costs with the incremental consequences of the different UPAVAN interventions. Cost-consequence analysis has been recommended for complex interventions, such as UPAVAN, that have multiple health and non-health effects which are difficult to measure in a common unit [65, 66]. Robustness of the analysis results will be assessed using sensitivity analyses. A full protocol will be developed *a priori* in an economic evaluation plan.

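### The cost-consequence listing is worded as costs and undefined significant outcomes, at odds with its own all-outcomes scope and with the limit on formal testing

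*Protocol article*

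**What the plan says.** The protocol article's Economic evaluation section describes the scope of the evaluation in four ways.

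- Its perspective is societal. It covers all costs to implementers, providers and households, and on the benefit side "all associated and measurable outcomes or benefits associated with the intervention".
- Its form is a cost-consequence analysis "comparing incremental costs of the interventions and incremental changes in the trial outcomes".
- The presentation rule is: "Incremental costs and significant outcomes will be listed separately", so that policymakers can set costs against consequences for the different interventions.
- The reason for choosing this form is that it suits complex interventions "that have multiple health and non-health effects which are difficult to measure in a common unit".

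The section ends by deferring full detail to an economic evaluation plan, which is not shown.

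The Analysis plan section says: "We will restrict formal testing, and reporting of *p* values, to the primary and secondary outcomes", with each intervention arm compared only with control. It adds: "All other outcomes will be reported and interpreted with caution". Effect sizes are to be given with 95% confidence intervals.

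Table 2 (Trial outcomes) has two primary outcomes (child dietary diversity, maternal BMI) and two secondary outcomes (maternal dietary diversity, child wasting). Agricultural production, household expenditure, and women's decision-making, time use and gender parity stand under other outcomes.

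**The concern.** A cost-consequence analysis is useful because it sets the whole range of consequences beside the whole cost and leaves the weighing to the reader. If a consequence enters the table only after passing a significance threshold, costs stay complete while consequences are selected. Three things follow. Outcomes with a null or imprecise result drop out of the table. Estimates that remain tend to be overestimates. And the three arms may show different sets of outcomes, so they cannot be read line by line.

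The last point matters here because the table is meant to help policymakers look across the interventions, while the Limitations section says the trial is not powered for differences between them and the Analysis plan excludes direct comparisons. An outcome listed for one arm and absent for another invites exactly that inference.

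The rule also lacks a basis for the non-health outcomes. They are part of the stated reason for choosing this form of evaluation, and the Analysis plan gives them no formal test.

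**Working it through.** **1. The statements side by side.**

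| Place | Which consequences count | Condition on test result |
|---|---|---|
| Economic evaluation, opening sentence | All that are associated and measurable | None |
| Economic evaluation, form of analysis | Incremental changes in the trial outcomes | None |
| Economic evaluation, presentation | Significant outcomes | Yes, if the word is statistical |
| Analysis plan | Tests and p-values for 2 primary + 2 secondary = 4 outcomes | Other outcomes reported without a formal test |

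Under the statistical reading, row three contradicts rows one and two. Combined with row four, only the four nutritional outcomes could qualify through a planned test. No agricultural, expenditure or empowerment outcome could.

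**2. Reproducing the plan's power figure.** The inputs come from the Sample size section: 37 clusters per arm, 24 children aged 6–23 months per cluster, intra-cluster correlation 0.06, 22% in control, a 9-point difference (so 31%) and a 5% level. Two-sided testing is my assumption.

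- Design effect: 1 + (24 − 1) × 0.06 = 2.38.
- Effective number per arm: 37 × 24 / 2.38 = 373.1.
- Standard error under no difference, pooled proportion 0.265: √(2 × 0.265 × 0.735 / 373.1) = 0.0323.
- Standard error under the alternative: √[(0.22 × 0.78 + 0.31 × 0.69) / 373.1] = 0.0321.
- Power: Φ[(0.09 − 1.96 × 0.0323) / 0.0321] = Φ(0.83) = 0.797.

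This agrees with the stated 80%. Nothing in this point changes that figure.

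**3. What a p < 0.05 filter would do (illustration only).** Let Z be the estimate divided by its standard error, normal with mean μ = 1.96 + z(power) and variance 1. The outcome is listed as a benefit if Z > 1.96.

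- At 80% power, μ = 1.96 + 0.84 = 2.80. Probability of omission: 1 − 0.80 = 0.20.
- Mean of Z given listing: μ + φ(1.96 − μ) / Φ(μ − 1.96) = 2.80 + 0.280 / 0.80 = 3.15.
- Average inflation: 3.15 / 2.80 = 1.125. A true 9-point effect would appear on average as 9 × 1.125 = 10.1 points when listed.

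| Power | Source | Omitted | Average inflation when listed |
|---|---|---|---|
| 80% | Sample size section | 20% | 1.12 |
| 50% | assumed | 50% | 1.41 |
| 30% | assumed | 70% | 1.81 |

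The lower two rows are assumptions, because the article gives no power for the other outcomes.

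**4. Different lists for different arms.** Suppose all three interventions have the same true effect, each with 80% power against the shared control arm. With equal arms, the three test statistics have pairwise correlation 0.5. From the trivariate normal distribution, the outcome is listed for all three arms with probability 0.61, for none with 0.05, and for some but not others with 1 − 0.61 − 0.05 = 0.34. In about a third of such trials, equally effective interventions would have different entries for that outcome.

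**The case against.** The strongest objection is that the sentence can be read harmlessly. It gives no threshold and does not speak of statistical significance. Significant may mean important, and the main message may simply be that costs and outcomes are shown separately and not combined into a ratio. The rest of the section points to all outcomes, and an economic evaluation plan is still to come.

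Much of this stands. A reader might infer that the article commits to a p-value filter and to nothing else in the table; that is an inference from an undefined word. But in a trial protocol the statistical sense is the natural one, and the article uses the term that way when it gives the level of significance in the Sample size section. If importance was meant, the rule is still an unstated selection that sits badly with the promised scope. The later plan does not remove the problem: it either inherits the published wording or departs from it.

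Two further readings go too far.

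- A reader might say the filter cannot be applied to the other outcomes. Significance could be read from the planned 95% confidence intervals, although that would bring back by another route the testing that the Analysis plan restricts.
- A reader might say null or harmful effects would be hidden. The Analysis plan commits to reporting the other outcomes, and a statistically significant harm would meet the filter. The gap would be in the economic table only.

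Household income should also be kept out of the argument. It is a hypothesised mediator; Table 2 lists expenditure.

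Finally, the inflation figures are generic and would fit any trial. They show direction and rough size under one reading and do not measure an error in this trial.

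**Conclusion.** The point holds as an undefined selection rule that is inconsistent with its own section and does not fit the Analysis plan. It is a stated rule and not merely an omitted detail, so it is worth correcting in the text. If significant means p < 0.05, a true effect with the stated 80% power would be missing from the economic table 20% of the time and overstated by about 12.5% on average when present. The agricultural production, expenditure and empowerment outcomes would have no planned test by which to enter it. These sizes rest on a two-sided 5% threshold, a normally distributed estimate, and listing in the favourable direction. The effectiveness results, the sample size and the power are unaffected.

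**What to change.** In the Economic evaluation section, delete the word significant and state the rule in full. For example: incremental costs and all pre-specified primary, secondary and other trial outcomes will be listed for each intervention arm against control, with estimate and 95% confidence interval, regardless of statistical significance. P-values would remain limited to the primary and secondary outcomes, as the Analysis plan already provides. Carry the same sentence into the economic evaluation plan.

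This changes one sentence and needs no new data or analysis. The only cost is a longer table.
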